### Data collection

For this study, data will be collected at the following 3 time points: 1) At the time of Baseline Visit (8–23 weeks of gestational age), women will undergo group assignment and complete the baseline data collection (Survey 1); 2) After 30 weeks gestational age, research nurses will meet participants prior to or after their prenatal care appointment to administer the second survey (Survey 2); and 3) Postpartum data collection will be conducted after women attend their postpartum visit and consist of medical chart abstraction, and will not require patient contact. The study surveys will be administered electronically. Patients’ medical information will be collected from the electronic medical record (EMR). Regular data review/reports will be generated through the EMR to monitor enrollment, group balance, and the timing of the reminder calls & patient incentives. The overall timeline for study visits and data collection is summarized in Table 2.

**Table 2 Tab2:** Data collection and outcome measurement

	Gestational age <23 week (Survey 1)	Gestational age 30+ week (Survey 2)	12-week Postpartum medical chart review
Birth outcomes and pregnancy complications			
Gestational age at delivery			X
Birth weight			X
APGAR scores			X
Admission to neonatal intensive care unit (NICU)			X
Intrauterine fetal demise			X
Neonatal death			X
Pre-eclampsia			X
Gestational hypertension			X
Gestational diabetes			X
Intrauterine growth restriction			X
Macrosomia (weight >4000 g.)			X
Hospital admission during pregnancy, reason			X
Induction and reason			X
Maternal behavioral and other measures			
Maternal smoking, alcohol and marijuana use	X	X	X
Physical activity, dietary intake, and multivitamin use		X	
Maternal psychosocial measures			
Patient activation measure (PAM)	X	X	
Prenatal planning and preparation coping		X	
Prenatal anxiety, and depressive symptoms	X	X	
Shift and Persist	X		
Discrimination in prenatal care		X	
Stress management		X	
Perceived family support	X		
Support from baby’s father & relationship with baby’s father		X	
Life stressor, financial stressor and housing instability in pregnancy		X	
Perceived stress and neighborhood safety	X		
Everyday discrimination scale	X		
Role of religious on dealing with stress	X		
Adverse childhood experience	X		
Interconception care			
Attendance at postpartum visit			X
Postpartum contraception use			X
Demographics			
Race and ethnicity	X		

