### Study outcomes

*The primary study outcome* is PTB (defined as birth at less than 37 weeks gestation).

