### Analytic plan

Primary analyses for Aims 1, 2, and 3 will be conducted using an intent-to-treat approach. Study participants will be retained in their original assignment groups after the randomization in the analysis regardless of the number of missed visits, the use of additional services (e.g., progesterone), or loss to follow-up.
*Aim 1 analysis plan*: comparison of primary and secondary outcomes for GPNC vs. IPNC. To test the hypothesis for aim 1 that women who participated in GPNC will have a lower rate of PTB and other selected birth outcomes as compared to their counterparts in IPNC, multivariate regression models (logistic regression if the outcome is a binary variable and linear regression if the outcome is a continuous variable) will be employed with the intervention assignment as the primary independent variable. We will test the null hypothesis of coefficient of main exposure variable (GPNC vs. IPNC) equals zero. Stratified analyses will be conducted (e.g. race/ethnicity, previous history of PTB) to compare the primary and other outcomes within sub-groups.
*Aim 2 analysis plan*: comparison of racial disparities of primary and secondary outcomes for GPNC vs. IPNC. To test the hypothesis for Aim 2 that the Black-White differences in PTB and other selected birth outcomes is smaller in the GPNC as compared with that in IPNC, we will apply analyses similar to Aim 1 but adding an interaction term of prenatal care (GPNC vs. IPNC) with race (White vs. Black). We will test the null hypothesis of coefficient of interaction term equals zero. For aim 2, only women identified themselves as either Black or White will be included in the primary analysis. Then, we will conduct a sensitivity analysis to see whether including women who self-identified race as “Hispanic ethnicity”, “Mixed race” and “Other race” will influence the primary analysis results. Such sensitivity analysis will be guided by the results from the sub-groups analysis in Aim 1.

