*Aim 3 analysis plan*: comparison the effects of GPNC on maternal psychosocial (i.e. activation, engagement, stress) and behavioral (i.e. smoking, healthy eating, healthy practices) changes and exploring whether improving maternal psychosocial and health behavior outcomes will explain the potential benefits of the GPNC on racial disparities in birth outcomes. To address Aim 3, we will first test whether changes in maternal health behaviors or psychosocial factors differ by intervention and race. To do this, a similar analytic plan as used in Aim 1 & 2 will be applied, however, the dependent variables will be changes of health behaviors or psychosocial factors from baseline (~20 weeks) visit to late pregnancy (30–36 weeks). If we observe any significant differences in these health behaviors or psychosocial factors by intervention or race, the next step is to explore whether and to what extent the differences in the intermediate health behavior or psychosocial factors could explain the intervention effect or racial disparities of birth outcomes. To do so, the main multivariate regression models will be examined with and without adjustment for the intermediate health behavior or psychosocial variables.

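### Aim 3 mediation of the preterm-birth effect compares logistic models with and without mediators that women delivering before Survey 2 cannot have, so unless both models use the same women the comparison can show or hide mediation falsely

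*Protocol article*

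**What the plan says.** All references are to the Protocol article.

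- **Outcome.** Under Study outcomes, the primary outcome "is PTB (defined as birth at less than 37 weeks gestation"; it is binary.
- **Main models.** Under Analytic plan, Aim 1, the models are "logistic regression if the outcome is a binary variable and linear regression if the outcome is a continuous variable". Aim 2 adds a treatment-by-race interaction. The PTB models are therefore logistic.
- **Mediation step.** Under Analytic plan, Aim 3, mediators are first compared by arm and race as "changes of health behaviors or psychosocial factors from baseline (~20 weeks) visit to late pregnancy (30–36 weeks" of gestation. If any differ significantly, the next step asks how far they "could explain the intervention effect or racial disparities of birth outcomes". The method is that "the main multivariate regression models will be examined with and without adjustment for the intermediate health behavior or psychosocial variables".
- **Timing of the mediators.** Under Data collection: "After 30 weeks gestational age, research nurses will meet participants prior to or after their prenatal care appointment to administer the second survey". Table 2 places activity, diet, coping and stress management at Survey 2 only. Patient activation, anxiety and depressive symptoms are at Surveys 1 and 2. Perceived stress is at Survey 1 only. Smoking, alcohol and marijuana use are at both surveys and also in the postpartum chart review.
- **Population.** The Analytic plan calls the primary analyses of all three aims intent-to-treat, including women lost to follow-up.

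The article does not say whether the two mediation models share a sample, or how women who deliver before Survey 2 are handled.

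**The concern.** The comparison treats the movement of a coefficient, once mediators are added, as the part of the effect that the mediators carry. Two other things can move it.

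1. **Selection on the outcome.** A birth before 37 weeks that precedes Survey 2 is a primary event with no late-pregnancy mediator value. The value is not merely unrecorded, because the pregnancy was over before the measurement was due. A model containing the mediator, fitted to the data as measured, omits that woman; the model without it keeps her. If group care affects early and later preterm births differently, the treatment odds ratio changes for that reason alone.
2. **Non-collapsibility.** In logistic regression, adding a predictor of the outcome shifts the treatment odds ratio even if the predictor is unrelated to treatment.

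At stake is the trial's account of why group care works and whether these factors explain the racial disparity. The Background presents this as a gap that the trial will fill.

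**Working it through.** **Plan's own figure.** The Sample size section takes control PTB 13%, RR 0.70, alpha 0.05 and power 90%, and states 1,356 per group. The two-proportion formula (13% vs 0.70 × 13% = 9.1%, two-sided, no continuity correction) returns 1,356. The article gives no figure for the mediation step.

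**Starting point.** In all women:
- OR = (0.091/0.909) / (0.130/0.870) = 0.670; log OR = -0.4005.
- Apparent proportion mediated = 1 - (adjusted log OR / unadjusted log OR).

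**(a) Unequal samples, mediator with no effect**

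Assumptions, not in the document: a share s of control PTB precedes Survey 2, and the RR for those early births is r. Overall risks stay at 13% and 9.1%.
- Early risks: e0 = s × 0.13; e1 = r × e0.
- Late risks: l0 = 0.13 - e0; l1 = 0.091 - e1.
- Odds of PTB among women undelivered at Survey 2 are l/(1 - p), where p is the overall risk. Hence OR = (l1/l0) × (0.870/0.909) = (l1/l0) × 0.957.

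Worked case, s = 15%, r = 0.4: e0 = 0.0195, e1 = 0.0078, l0 = 0.1105, l1 = 0.0832. OR = 0.753 × 0.957 = 0.721; log OR = -0.3276. Apparent proportion mediated = 1 - 0.3276/0.4005 = 18%.

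| Share of control PTB before Survey 2 | Early RR 0.4 | Early RR 0.70 | Early RR 1.0 |
|---|---|---|---|
| 15% (26 control events of 1,356 women) | OR 0.721, 18% | OR 0.670, 0% | OR 0.619, -20% |
| 25% (44 events) | OR 0.766, 33% | OR 0.670, 0% | OR 0.574, -39% |
| 40% (71 events) | OR 0.861, 63% | OR 0.670, 0% | OR 0.479, -84% |

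Percentages are the false proportion mediated. Its sign depends on whether group care works better or worse on early births than on later ones.

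**(b) Non-collapsibility, same women in both models, no mediation**

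The mediator is standard normal and independent of arm, with log-odds slope b per SD. Solve for the intercept and the treatment coefficient so that the averaged risks are 13% and 9.1%.

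| Mediator OR per SD (assumed) | Adjusted OR | Apparent proportion mediated |
|---|---|---|
| 1.25 | 0.669 | -0.5% |
| 1.65 | 0.663 | -2.5% |
| 2 | 0.657 | -5.0% |
| 3 | 0.636 | -13.1% |

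The adjusted OR always moves away from 1, so this part can only hide mediation. Where half the risk reduction is truly mediated and the mediator OR is 2 per SD, the comparison gives 43.6% against a true 46.4% on the log-OR scale. Linear models, such as that for birth weight, do not have this problem.

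**The case against.** - **The sample mismatch is inferred.** A reader might conclude that the plan fits its two models in different women. It does not say so. A common sample and the handling of missing mediators could stand in an analysis plan that is not shown. This stands, so the point is conditional. The stated method nevertheless needs that condition, and a common sample would limit the result to women undelivered at Survey 2, which the article does not mention.
- **The bias may be nil.** This is correct if the RR is the same early and late. The article gives neither the share of PTB before Survey 2 nor the RR by timing.
- **Non-collapsibility is minor.** This is also right. A reader might take it as the main defect, but the shift reaches -13% only at an OR of 3 per SD, and nothing in the document suggests that a survey scale predicts PTB so strongly. The significance step would also screen out many mediators unrelated to arm, although one that differs only by race would pass.
- **Not every mediator is lost.** Smoking, alcohol and marijuana use may be partly recoverable from chart review. The psychosocial scales are not.
- **The step is exploratory.** The article says so. A reader might infer that the mediation results are worthless or that the main effectiveness tests are compromised. Neither follows: the Aim 1 and Aim 2 tests do not use the mediators.

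**Conclusion.** The concern holds in conditional form. For PTB, Aim 3 reads mediation from a pair of logistic models, and most of the mediators cannot exist for women who deliver before Survey 2. If the two models use different women, the difference between them mixes mediation with selection on the primary outcome. At 13% vs 9.1% PTB, with 15% to 40% of control PTB assumed to precede Survey 2, the false proportion mediated is 18% to 63% at an early RR of 0.4, -20% to -84% at 1.0, and zero at 0.70. Those shares and early RRs are assumptions chosen to show the range. Non-collapsibility adds about -0.5% to -5% for mediator ORs of 1.25 to 2 per SD. It can only hide mediation, and only for outcomes analysed by logistic regression. The point warrants a change to the exploratory analysis and to how its result is described.

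**What to change.** In the Aim 3 paragraph of the Analytic plan:

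1. Fit the models with and without mediators in the same women: those still pregnant at a fixed, stated landmark with Survey 2 done. Use PTB after the landmark as the outcome.
2. Compare total and direct effects on the risk-difference scale by standardisation. Adjust for baseline mediator values where Survey 1 holds them, and for measured mediator-outcome confounders. Table 2 has no baseline value for diet, physical activity, coping or stress management, and no Survey 2 value for perceived stress.
3. State that the result is exploratory, applies only to pregnancies reaching the landmark, excludes earlier preterm births, conditions on a post-randomisation state, and assumes no unmeasured mediator-outcome confounding.

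The cost is revised wording and some extra programming. No new data are needed and the sample size does not change. The loss of events is real: at the planned rates and 1,356 per arm, a 15% to 40% share of control PTB before the landmark removes about 26 to 71 control events, plus those in the group-care arm.

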### Statistical review and interim analyses

Statistical review of the study will be conducted by a statistician periodically during the intervention phase of the study. Interim analyses will be performed to assess outcomes and to decide the continuation, alteration of study design, or early termination, as appropriate. For each of the hypothesis tests considered in this proposal, we plan to monitor the change of the power after having a reasonable number of patients (e.g. 50%) in each group. In addition, some Monte Carlo simulations might be adopted to get more accurate power estimates. If the power reaches the desired level and is quite stable as more patients are included gradually, we might stop collecting new data. Such interim analyses will also be used to monitor the patients’ safety and data quality.

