### Sample size

We calculated our sample size based on Aims 1 & 2 with the primary outcome of PTB. Based on the literature and our preliminary data, the rate of PTB was approximately 10-16% of women in the traditional care setting [16]. The odds ratio of comparing PTB in GPNC to IPNC was 0.67 in the Ickovics study and 0.53 in our own study [16, 17]. Our own work also suggests that the risk difference of having PTB between Black women and White women was 1.0% in the IPNC and 2.4% in the GPNC. Taken together, it is reasonable to assume that the relative risk of PTB in the IPNC group could range from 10% to 16%. For aim 1, assuming the proportion of PTB rate of 13%, our study will need *N* = 2,712 (1,356 in each group) to detect the relative risk of PTB in GPBC vs. IPNC of 0.70 with an alpha of 0.05 and a power of 90%. For aim 2, assuming the proportion of PTB rate of 0.02, our study will need *N* = 2,748 (1,374 in each group) to detect reduction in risk difference of 1.4% between Black and White women in GPNC vs. IPNC group with an alpha of 0.05 and a power of 90%. With an estimated 15% attrition rate, we will target recruiting 3,160 (*N* = 1,580 in each group) women for this study. Table 3 gives the estimated minimum number (in each group) required to achieve an alpha of 0.05 and a power of 80% or 90% to detect the risk ratio from 0.5 to 0.7 in Aim 1 and to detect the risk difference from 0.01 to 0.08, given the rate difference (P_0_) of preterm birth between Black women and White women at the IPNC group ranges from 2% to 3% in Aim 2, This sample size estimates that the proposed study will have 90% power to detect racial difference on PTB for Aim 2.

**Table 3 Tab3:** Sample size and power calculations

	Power = 80%			Power = 90%		
Aim 1	RR = 0.50	RR = 0.60	RR = 0.70	RR = 0.50	RR = 0.60	RR = 0.70
P_0_ = 0.10	435	721	1,356	582	965	1,814
P_0_ = 0.13	326	540	1,014	436	723	1,356
P_0_ = 0.16	258	427	800	345	571	1,070
Aim 2	RD = 0.01	RD = 0.014	RD = 0.018	RD = 0.01	RD = 0.014	RD = 0.018
P_0_ = 0.02	2,319	1,027	526	3,103	1,374	704
P_0_ = 0.03	3,826	1,799	995	5,121	2,048	1,332
P_0:_ the RD of PTB in IPNC group; RR: relative risk						

Abbreviation: RD = risk difference

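### The interim section lets data collection stop when an undefined "power" reaches an unstated level, with no control of the 0.05 error rate

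*Protocol article*

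**What the plan says.** In the protocol article, under Statistical review and interim analyses, the purpose of the looks is stated as follows: "Interim analyses will be performed to assess outcomes and to decide the continuation, alteration of study design, or early termination, as appropriate". The quantity to be followed is power: "For each of the hypothesis tests considered in this proposal, we plan to monitor the change of the power", starting once a reasonable share of patients, for example 50%, is in each group. The stopping criterion is "If the power reaches the desired level and is quite stable as more patients are included gradually, we might stop collecting new data". Simulation may be used to refine the power estimates.

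The section does not say what effect the power is calculated at, what level is wanted, how many looks there are, which hypothesis governs stopping, or how the final test allows for the looks. The Sample size section plans Aim 1 "to detect the relative risk of PTB in GPBC vs. IPNC of 0.70 with an alpha of 0.05 and a power of 90" per cent, with no allowance for interim analyses. Its Table 3 also lists 80% power. The Analytic plan tests the treatment coefficient against zero and likewise mentions no adjustment.

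**The concern.** Power recalculated at the effect seen so far is a one-to-one function of the interim test statistic. Stopping because that power is high is then stopping because the interim p-value is small. Doing so at repeated looks, and then testing at an unadjusted 0.05, does not in general keep the error rate at 0.05. The estimate in a trial that stops this way also tends to be too favourable. At stake are the p-value and confidence interval for preterm birth, the primary outcome, and a decision on when to stop that cannot be repaired once data collection has ended.

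**Working it through.** **Inputs.** From Sample size: control preterm birth rate 13%, relative risk 0.70 (so 9.1% in group care), alpha 0.05, power 90% (80% also tabulated), 1,356 per group for Aim 1 and 1,374 for Aim 2. From the interim section: first look at about half the patients, then repeated. Assumed, because not stated: a two-sided test; 1, 5 or 10 interim looks between 50% and 100%; an unadjusted |Z| > 1.96 test wherever the trial stops.

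**The plan's own figure.** Write p̄ = (p0 + p1)/2. The pooled-variance formula is n = [1.96 √(2p̄(1−p̄)) + 1.2816 √(p0(1−p0) + p1(1−p1))]² / (p0 − p1)².
- Aim 1: p0 = 0.13, p1 = 0.091, p̄ = 0.1105 gives 1,355.9, so 1,356 per group.
- Aim 2: 0.02 versus 0.006 gives 1,373.6, so 1,374 per group.

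Both match exactly, so the plan uses a two-sided 0.05 test with no alpha set aside for looks.

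**What the rule means as a threshold.** Let t be the fraction of information available and Z the test statistic at that point. For a 90% level:
- (a) Observed power at the current n: stop if |Z| ≥ 1.960 + 1.282 = 3.24.
- (b) Observed effect projected to the full sample: stop if |Z| ≥ 3.24 √t, which is 2.29 at t = 0.5.
- (c) Conditional power under the current trend: stop if |Z| ≥ √t (1.960 + 1.282 √(1−t)), which is 2.03 at t = 0.5.
- (d) Power from the pooled event rate at a fixed relative risk of 0.70: the threshold does not involve the between-arm difference.

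**Type I error, Aim 1 test, nominal 5%.** Readings (a) to (c) were simulated as Brownian motion with 400,000 replicates and (d) with binomial data. Ranges run over 80% and 90% levels and over the numbers of looks. The last column requires two consecutive looks above the threshold, as one way to enforce stability, with 5 or 10 looks.

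| Reading | Stop at first crossing | Two consecutive crossings |
|---|---|---|
| (a) observed power, current n | 5.0-5.4% | 5.0-5.1% |
| (b) projected to full N | 6.2-9.2% | 5.3-7.1% |
| (c) conditional power | 7.7-10.3% | 6.5-8.9% |
| (d) pooled rate, fixed RR | about 5% | not run |

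Binomial simulation at 1,356 per arm, with up to 50 interim looks, gave similar first-crossing figures: 5.0-5.4% for (a), 6.2-10.0% for (b) and 7.7-10.6% for (c).

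**Exaggeration in trials that stop early.** With the planned effect true (drift 3.24), a 90% level and first crossing, the mean log relative risk among stopped trials is too large by 65%, 40% and 37% under (a), 35%, 28% and 27% under (b), and 28%, 17% and 15% under (c), for 1, 5 and 10 looks respectively. The range is therefore 15-65%. Since 0.70^1.15 = 0.66 and 0.70^1.65 = 0.56, a true relative risk of 0.70 would be reported as about 0.66 to 0.56. Averaged over all trials, stopped or not, the binomial simulation gives about 0.68. Under (d) there is no exaggeration.

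**The case against.** The strongest reply is that the text does not say the power is observed. Updating it from the pooled rate at a fixed relative risk would be harmless, and boundaries are often left to an analysis plan that is not shown here. This stands in part. The outcome-based reading is an inference. It is the better one because the looks are meant to assess outcomes and decide on early termination, and because power at a fixed effect and rate would simply rise with n and need not settle. Nor is the point one of omission: the article states a stopping criterion, and that criterion is not an efficacy boundary.

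Further points in the plan's favour:
- **A strict threshold.** Observed power at the current n with a 90% level behaves like a boundary at |Z| ≥ 3.24 and adds almost nothing to the error (5.0-5.1%). This stands.
- **Stability.** The text requires power to settle as well as to reach the level. This stands and lowers the figures, as the table shows.
- **Delivery lag.** If only enrolment stops, pregnancies in progress still contribute. Assuming 0.2 of the total information arrives after stopping, first-crossing error falls to about 5.5-6.0% under (b) and 5.7-6.2% under (c). The text does not say whether follow-up would continue.
- **Exaggeration.** Any early efficacy stop has it. An O'Brien-Fleming-type look at 50% shows about 55% among stopped trials under the planned effect. It is therefore only a secondary argument.

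Masking the analysts to group assignment does not answer the concern, because a coded comparison of the two arms drives the same rule.

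A reader might also infer that Aim 2 could never reach the wanted power, or that monitoring several hypotheses must raise the error. Neither is supported. Power computed from the interim effect can cross any level by chance. The article does not say whether one test or all tests must reach the level, and requiring all would make stopping rarer.

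**Conclusion.** The point holds as a defect in a stated rule: a discretionary, repeated, outcome-related stopping criterion without a definition or error control. Its effect on type I error ranges from none to about double the nominal rate, and the document does not settle where in that range the trial lies. The figures cover the Aim 1 test alone. They rest on the two-sided test, the assumed looks and the 80-90% level; readings (a) to (c) also assume that power is computed from the between-arm difference. A reader might infer that the rule certainly inflates the error rate. The text does not support that, because the pooled-rate reading leaves the rate at 5% and the observed-power reading at 90% leaves it nearly so. The rule should be corrected before any look takes place, because its validity depends on a definition the article does not give.

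**What to change.** Delete the sentence that allows stopping on attained power, and put one of two things in its place.

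1. **No efficacy stop.** Monitor only the blinded pooled preterm birth rate and attrition, to check the planning assumptions. This leaves type I error at about 5%.
2. **A formal efficacy look, if early stopping is wanted.** Prespecify an alpha-spending boundary for Aim 1 preterm birth only, and state that Aims 2 and 3 cannot stop the trial. One example is a single Lan-DeMets O'Brien-Fleming-type look at 50% of outcomes: |Z| ≥ 2.963 (two-sided p about 0.003) at the look and |Z| ≥ 1.969 (p about 0.049) at the end. Other valid boundaries would serve.

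The cost is a change of wording and less freedom to stop early. For the example boundary, keeping 90% power multiplies the sample size by 1.003, from 1,356 to 1,361 per group; without that increase the loss of power is negligible. Option 2 protects the error rate but does not remove the exaggeration in a trial that stops early, so such an estimate should be reported with that caution.
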